#### Participants

Participants were recruited in four areas: Yorkshire and the Humber, Greater Manchester, Newcastle and Gateshead, and Northwest London.

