#### Randomisation and blinding

Following consent and baseline data collection, participants were individually randomised (1:1) to the symptoms clinic plus usual care or usual care alone, using a computer generated pseudorandom list, stratified by study centre with random permuted blocks of varying sizes. Allocation was concealed using a centralised web-based randomisation system.

The participant was then randomised and informed of their allocation. If assignment was to the intervention, the first symptoms clinic appointment was scheduled. If assignment was to usual care alone participants were reminded to use their usual healthcare services (eg, usual care GP) as required.

Due to the nature of the intervention, it is not possible to blind participants to their allocation. For practical reasons such as coordinating symptoms clinic appointments and ER-GP supervision some members of the research team are not blinded, including the trial manager and chief investigator (CI).

Members of the trial steering committee (TSC), study statisticians, health economists and those collecting outcome data are blinded to treatment allocation while the trial is ongoing.

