#### ER-GP recruitment, training and supervision

Seven ER-GPs were recruited and trained to deliver the symptoms clinic. Two withdrew because of competing demands, one after seeing fewer than 5 patients and one before seeing any.

Training comprised a mixture of small group sessions (both didactic and interactive), protected time to conduct and reflect on symptom clinic consultation techniques in practice and one-to-one or small group supervision. It involved 13 half-day sessions. Sessions 1–4 were two full days of training. Sessions 5–7 and 9–11 comprised protected time to see patients of the GPs own practice using newly learnt skills and reflection on this. Sessions 8 and 12–13 were training sessions focusing on consolidating skills and knowledge. In sessions 9–11 each ER-GP recorded a set of three consultations for review, quality assessment and constructive feedback by a panel comprising the CI and two other investigators.

During the study, ER-GPs received supervision with one of the investigators approximately every 1–2 months. Supervision included review of consultation content and encouraged reflective learning and consolidation of existing knowledge and skills and learning of new knowledge and skills.

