### Sample size

In the pilot trial, we observed an average 3.2 point clinically important change in the intervention group from baseline to 13 weeks, compared with a 1.4 point change in the control group. We have thus powered the trial on a between group difference of two points on the PHQ-15 (equivalent to a clinically important three point change from baseline).

We have based calculations of effect size on a pooled SD of 5; this is larger than that seen in our preliminary studies owing to their restricted eligibility range and more in keeping with observational studies. This results in a standardised effect size of 0.4, which is similar to that seen in two small European studies of extended GP consultations for broadly comparable patients.^37 38^

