#### Calculation of sample size

Allowing 25% lost to follow-up, and a further pragmatic 6% inflation to allow for minor treatment centre imbalances or differences, a sample of 188 patients per arm has 90% power (alpha=0.05) to detect this effect. The initial recruitment target was thus 376 participants. In October 2021, this was reduced in discussion with the funder, to 350 because lost to follow-up at 52 weeks postrandomisation was 18% rather than the anticipated 25%.

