### Data analysis

The primary outcome will be analysed using a partially nested heteroscedastic mixed-effects model to account for clustering by clinic GP. Secondary outcomes will be analysed in a similar manner within a generalised linear modelling framework using appropriate link functions for the outcomes’ distributions. Models will adjust for sex, age, whether the intervention was delivered in person or online, and baseline values of outcomes. A repeated measures analysis on PHQ-15 at all four measurement points will be conducted as a further secondary analysis using a multilevel growth curve model with time as a quadratic term, and a treatment-time interaction included in the model.

Intention-to-treat analysis will be used for the primary analysis of all outcomes, with complier average causal effect analysis as a secondary analysis. The primary outcome will be analysed using observed data with no imputation for missing data, but we will assess the amount and patterns of missing data and test the sensitivity of estimates of treatments effects using an appropriate imputation strategy such as multiple imputation by chained equation. We will explore potential modification of the treatment effect by including treatment-by-subgroup interactions in models. All treatment effect estimates will be presented with 95% CIs in forest plots.

A single main analysis will be performed at the end of the trial when follow-up is complete. Interim analyses will be performed if requested by the data monitoring and ethics committee (DMEC) and the trials unit SOPs will be adhered to maintain the integrity of the trial.

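### Randomisation is stratified by study centre but the stated covariate list omits centre, so the standard error is somewhat too large if centre is prognostic

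*Protocol article*

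**What the plan says.** The Randomisation and blinding section of the Protocol article describes 1:1 individual allocation from a list "stratified by study centre with random permuted blocks of varying sizes". No other stratification factor is named. Under Participants: "Participants were recruited in four areas: Yorkshire and the Humber, Greater Manchester, Newcastle and Gateshead, and Northwest London". I take these four areas to be the study centres, which is an assumption.

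The Data analysis section defines the primary model: "The primary outcome will be analysed using a partially nested heteroscedastic mixed-effects model to account for clustering by clinic GP". The covariates follow: "Models will adjust for sex, age, whether the intervention was delivered in person or online, and baseline values of outcomes". Secondary outcomes are to be modelled in a similar way. Nowhere does the article add centre as a fixed or random effect.

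Centre is otherwise taken into account only under Calculation of sample size, which includes "a further pragmatic 6% inflation to allow for minor treatment centre imbalances or differences".

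**The concern.** Permuted blocks within centre keep the arms nearly balanced in every centre. Differences between centres in mean outcome therefore largely cancel from the treatment comparison and add almost nothing to the true sampling variance of the estimate. A model without centre does not know this: it leaves the between-centre variance in the residual and reports a standard error that is too large. The usual remedy is to include the stratification factor in the model.

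The clinic-GP effect does not do this job. In a partially nested model it applies to intervention participants only, so it cannot absorb centre differences among controls.

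What is at stake is precision: in a superiority trial, an over-stated standard error gives away some of the benefit of stratifying and slightly raises the chance of missing a real effect.

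**Working it through.** **Inputs from the Protocol article.** Difference of 2 points ("We have thus powered the trial on a between group difference of two points on the PHQ-15"); SD of 5 ("We have based calculations of effect size on a pooled SD of 5"); alpha 0.05, taken as two-sided; 90% power; 25% anticipated loss; 6% inflation; 188 per arm. The revised target is 350, with 18% loss.

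**The plan's own figure.** Normal approximation: n = 2 × (1.960 + 1.282)² × 5² / 2² = 131.3, so 132 per arm; 132 / 0.75 × 1.06 = 186.6, so 187. The t-based version gives 133 per arm; 133 / 0.75 × 1.06 = 187.97, so 188. The stated sample size reproduces and is not at issue.

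**Precision at the revised target.** 350 × 0.82 = 287 analysed, or 143.5 per arm. SE = 5 × √(2/143.5) = 0.590. Power = Φ(2/0.590 − 1.960) = Φ(1.428) = 92.3%.

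**Effect of omitting centre in a simple model.** Let R² be the share of residual PHQ-15 variance lying between centres. The documents do not give it, so 2%, 5% and 10% are assumed, with the SD of 5 taken as the residual SD before centre is added. With balance within centres:

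- true SE = model SE × √(1 − R²), so over-statement = 1/√(1 − R²)
- true two-sided alpha = 2 × [1 − Φ(1.960/√(1 − R²))]
- power without centre = Φ(1.428/√(1 − R²))
- power with centre = Φ(3.388/√(1 − R²) − 1.960), where 3.388 = 2/0.590 before rounding

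| R² | SE over-stated by | True alpha | CI coverage | Power without centre | Power with centre |
|---|---|---|---|---|---|
| 0 | 0% | 5.0% | 95.0% | 92.3% | 92.3% |
| 2% | 1.0% | 4.8% | 95.2% | 92.5% | 92.8% |
| 5% | 2.6% | 4.4% | 95.6% | 92.9% | 93.5% |
| 10% | 5.4% | 3.9% | 96.1% | 93.4% | 94.6% |

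**The planned partially nested model, illustration only.** Of seven GPs trained, "Two withdrew because of competing demands, one after seeing fewer than 5 patients and one before seeing any", so six saw patients. A simulation (350 randomised, 18% loss, REML, normal reference, 1,500 runs per setting) assumed that each of the six worked in one centre only and that there was no true GP variance. Here the between-centre share is of total outcome variance, as the simulation has no other covariates.

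| Between-centre share | Type I error without centre | Type I error with centre | Power without centre | Power with centre |
|---|---|---|---|---|
| 0 | 0.043 | 0.040 | 91.4% | 89.3% |
| 1% | 0.036 | 0.040 | 89.9% | 89.7% |
| 2% | 0.033 | 0.040 | 87.3% | 89.9% |
| 5% | 0.017 | 0.040 | 78.3% | 90.7% |
| 10% | 0.005 | 0.040 | 64.3% | 91.9% |

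Under that assumption, centre differences are read as GP variance, which feeds directly into the standard error of the treatment effect. The Monte Carlo standard error of a rate near 0.04 is √(0.04 × 0.96/1500) = 0.005, so little should be read into the type I differences at 1% and 2%.

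With a GP intraclass correlation of 0.02, type I error with centre included was about 0.065. That excess comes from having only six GPs with a normal reference distribution. It is a separate matter that adding centre does not cure.

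**The case against.** The strongest reply is that this is small and errs on the safe side. In the simple model, power without centre stays above the planned 90% throughout the range examined. A centre effect would also have to survive adjustment for baseline PHQ-15 in a sample restricted at entry to scores of 10 to 20. This stands: the point concerns efficiency.

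A second reply is that the 6% inflation already provides for centre. In power terms it partly does: a 6% larger sample offsets a standard-error inflation of √1.06 = 1.030, equivalent to R² = 1 − 1/1.06 = 5.7% in the simple model. Taking the 6% out again at the revised target still leaves 90.8% power. But a larger sample does not make the reported standard error right.

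A third is that a condensed article may leave centre to the SAP. That would be fair had covariates been deferred, but the article gives a specific list. If the SAP does include centre, the two documents need to be brought into line.

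Two stronger readings are tempting. A reader might infer that the trial's intervals and p-values are invalid, with false positives in prospect. The documents do not support this: omitting centre acts conservatively, and only if centre is prognostic. A reader might also infer that centre differences will load onto the clinic-GP variance, with the large power losses in the second table. That requires GPs to be tied to centres. The article says only that, before March 2020, clinics were held in local practices or community research facilities. It gives no mapping of GPs to areas, and consultations later moved to video or telephone.

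**Conclusion.** The point holds as a modest, conditional loss of precision. The sole stratification factor is absent from an explicit covariate list, and no other model term stands in for it. If centre explains 2% to 10% of residual variance, the simple-model standard error is 1.0% to 5.4% too large, true alpha is 4.8% to 3.9%, and the power forgone is about 0.3 to 1.3 percentage points. If centre explains nothing, nothing is lost. The treatment estimate is unbiased in either case, and the omission does not raise the false-positive rate.

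These figures rest on an assumed between-centre share, on the SD of 5 as residual SD, and on 287 analysed. A larger loss in the partially nested model is possible but rests on an unstated link between GPs and centres, so it should not be presented as a finding.

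**What to change.** Add study centre, as used in the randomisation system (taken here as the four recruitment areas), as a fixed effect in the primary and secondary outcome models, and amend the covariate list in the Data analysis section to say so. Keep the 6% inflation as a sample-size allowance; it does not replace the adjustment.

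The cost is about three degrees of freedom out of roughly 287 analysed, and no new data, since centre was needed to randomise. If GPs did turn out to be tied to centres and centre had no effect at all, the simulation suggests a small price in the planned model: 89.3% power with centre against 91.4% without.

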### Process evaluation

The process evaluation comprises three nested observational studies, including consultation content analysis and interviews with participants and key stakeholders.

#### Consultation content analysis

A sample of approximately 30% of consultations are transcribed. These will be used to examine the intervention content using the classification of consultation content, explanations and response to explanation which we have developed from the preliminary studies.^19 20 39^ We will use this data to conduct exploratory analysis relating to explanation type, content and negotiation to patient outcomes in order to develop better understanding of the mechanisms by which the intervention affects outcomes.

#### Participant and stakeholder interviews

To explore processes of change within participants, semistructured interviews are conducted with a purposive sample of participants at different stages of the intervention. Only participants who did not have their consultations transcribed were invited for interview, and an even distribution was sought between patients with pain and fatigue type symptoms, and working and non-working patients. Interviews will be transcribed and analysed thematically, recognising that there are likely to be changes in intrapersonal understanding and interpretation (for which an interpretive phenomenological approach is likely to be valuable) and interpersonal or social understanding and interaction. Particular attention will be paid to patients’ views on what aspects of the Symptoms Clinic were particularly valuable to them and how these translated into perceived changes in thoughts, behaviours and symptoms.

Stakeholder interviews will examine acceptability of the clinic concept and processes, skills learnt and knowledge transferred, value for GPs and perceived value to patients.

#### Relationship between process evaluation and intervention delivery

Medical Research Council (MRC) guidance on process evaluation highlights the importance of considering the relationship between process evaluation and intervention delivery^40^ including whether the process evaluation is allowed to inform the intervention or the two are independent of each other. Information was permitted to flow from the process evaluation to the intervention during the first 3 months of symptoms clinic delivery. These can be considered as the time of professional learning curves for both the ER-GPs and the supervising investigators. During this time early lessons can be learnt and shared.

### Health economics

We will conduct a cost-effectiveness analysis (CEA) of the symptoms clinic plus usual care compared with usual care alone from the primary perspective of the UK NHS and personal social services. This will be based on HCRU (including primary and secondary care contacts such as GP consultations, diagnostic tests and investigations, physical and mental health specialist referrals, and prescription psychotropic and pain-related medications) and outcome data collected during the trial. It will take the format of a within-trial CEA and use a cost-utility framework to estimate cost per quality-adjusted life-year (QALY) gained.

The effects of the intervention will be estimated as gain in QALYs at 52 weeks using health-related quality of life data collected at baseline, 13, 26 and 52 weeks and the area under the curve method. Published UK tariffs will be used to convert these data to quality of life weights.

We will measure preference-based health-related quality of life using the EQ-5D-5L and the SF-6D. We will also use the newer capability well-being ICECAP-A measure to examine their relative responsiveness to change in this patient population.

A self-reported healthcare resource use questionnaire will be administered at 26 and 52 weeks postrandomisation to estimate healthcare resource use costs.

Data from GP electronic records at 52 weeks postrandomisation will be collected, where available and used for cross validation with self-reported data. Data from GP records will be extracted onto a standardised data collection form.

Use of healthcare resources will be valued and the associated costs estimated by assigning unit costs from standard published UK sources (including personal social service research unit unit costs, NHS reference costs, British National Formulary). Costs related to intervention delivery will be estimated using trial records, taking into account:

Face-to-face/video consultation clinic time.Clinic-related administration.Clinician training,Clinical supervision.

The CEA will be performed on an intention to treat basis (for participants with complete data on resource use and health utilities across all follow-up time points). The results of the analysis will be reported as incremental costs, effects and incremental cost-effectiveness ratios in terms of the incremental cost per QALY gained.

Generalised linear regression analyses will be used to estimate the differences (and associated 95% CIs) in per patient mean total costs and differences in mean total QALYs comparing the symptoms clinic intervention plus usual care compared with usual care alone, adjusting for baseline differences in cost, utility and other patient characteristics (eg, age, gender, PHQ-15 score). Uncertainty will be explored by conducting a range of one-way and multiway deterministic sensitivity analyses (or probabilistic sensitivity analysis if more appropriate) to test the robustness of the base case results including assuming a broader cost perspective (eg, including private healthcare costs), evaluating the effect of missing values (comparing results based on complete cases and those estimated using multiple imputed values) and potential bias due to high-cost patients (removing these expensive participants from the analysis). Cost per QALY data will also be presented in the form of cost-effectiveness acceptability curves to show the probability that the intervention is cost effective for different values of willingness to pay per additional QALY.

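### The base-case cost-effectiveness analysis is labelled intention to treat but is a complete-case analysis, with multiple imputation kept as a sensitivity analysis

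*Protocol article*

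**What the plan says.** The Health economics section of the protocol article plans a within-trial cost-utility analysis. It fixes the analysis set in one sentence: the CEA is done on an "intention to treat basis (for participants with complete data on resource use and health utilities across all follow-up time points". The sentence after it says that this analysis supplies the reported incremental costs, effects and cost per QALY.

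The same section then lists sensitivity analyses "to test the robustness of the base case results including assuming a broader cost perspective". One of them is "evaluating the effect of missing values (comparing results based on complete cases and those estimated using multiple imputed values".

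Three further statements show what complete data would require:

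- QALYs come from "health-related quality of life data collected at baseline, 13, 26 and 52 weeks and the area under the curve method".
- For costs, "A self-reported healthcare resource use questionnaire will be administered at 26 and 52 weeks postrandomisation".
- GP records are collected "where available and used for cross validation with self-reported data". They are not described as a way to fill gaps.

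On follow-up, the Calculation of sample size section reports, for October 2021, that "lost to follow-up at 52 weeks postrandomisation was 18% rather than the anticipated 25" per cent. The abstract gives 354 randomised.

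The Data analysis section also uses the intention-to-treat label. It analyses the primary clinical outcome on observed data and tests imputation as a sensitivity analysis.

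**The concern.** Analysing people in the arm to which they were allocated is one part of intention to treat. Keeping the randomised sample together is another, and the CEA sentence gives that part up. A participant leaves the base case because of something that happens after randomisation: a missed form. One missing utility removes everything else that the participant reported, including observed costs and utilities at other visits.

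Cost-effectiveness is named alongside clinical effectiveness in the trial's primary aim, so the base-case cost per QALY is a headline result. As planned, it would come from the smaller data set and the stronger missing-data assumption, while the analysis that uses all the observed follow-up stands behind it as a check. Participants know their allocation and the utilities are self-reported, so one cannot assume that completeness is unrelated to arm or health.

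**Working it through.** **1. Which analysis is the base case?** The analysis set sentence limits the CEA to complete data, and the next sentence takes the reported ratios from that analysis. The sensitivity paragraph tests the base-case results by, among other things, "comparing results based on complete cases and those estimated using multiple imputed values". Read together, complete case is the base case and imputation is secondary.

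**2. What must a participant supply?**

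- Utilities at 13, 26 and 52 weeks (baseline is collected at enrolment, before randomisation).
- Resource use at 26 and 52 weeks.

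The primary clinical comparison needs only the PHQ-15 at 52 weeks and the baseline values.

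**3. Upper limit on the analysis set.** The plan gives no number for the CEA set, so there is no stated figure to reproduce. Inputs: 354 randomised (abstract); 18% lost at 52 weeks (Calculation of sample size). Assumptions: the October 2021 rate holds for the final sample, and a person lost at 52 weeks has no 52-week utility or resource-use data.

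- Maximum complete = 354 × (1 − 0.18) = 290.3, about 290.
- Excluded = 354 × 0.18 = 63.7, about 64.

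**4. Below the limit.** Let *e* be the share of 52-week responders who lack a 13- or 26-week utility or some resource-use data. The documents give no value; 5% to 20% is assumed. Complete = 354 × 0.82 × (1 − *e*).

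- *e* = 5%: 275.8, about 276 (77.9% of 354).
- *e* = 10%: 261.3, about 261 (73.8%).
- *e* = 20%: 232.2, about 232 (65.6%).

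**5. What the CEA loses beyond the clinical analysis.** The primary clinical analysis also has a limit of about 290, because it too uses observed 52-week data. The additional exclusions are 290.3 − 275.8 = 14.5 to 290.3 − 232.2 = 58.1, so about 15 to 58 people over the assumed range.

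**6. What each analysis assumes.** The planned regression adjusts for baseline cost, utility and characteristics such as age, gender and PHQ-15.

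- Complete case: unbiased if completeness is unrelated to total cost and QALYs, given allocation and those covariates.
- Multiple imputation: missingness may also depend on the costs and utilities observed at the visits that were completed.

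Someone who reports a poor 26-week utility and then stops replying can be accommodated under the second condition but not, in general, under the first.

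**The case against.** The strongest reply has five parts.

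- **The label follows the article's own usage.** The Data analysis section also says intention to treat and then uses observed data without imputation. There the term means analysed as allocated, and the CEA states its restriction openly. This stands in part: no reader is deceived. But the term still describes an analysis that excludes randomised people for incomplete follow-up at any of three visits.
- **The check is already planned.** The complete-case and imputed results will be compared, so a discrepancy would be seen. This stands and limits the harm. It does not settle which result is the headline.
- **Bias is not shown.** This stands. A reader might infer that the base-case cost per QALY is biased. The documents do not show that incomplete participants differ, that completeness differs by arm, or which way an error would run. Non-responders are chased, and there is a voucher at 52 weeks.
- **The loss may be smaller than feared.** A reader might multiply assumed response rates as if visits were missed independently, for example 0.85 × 0.83 × 0.82 = 0.58, and conclude that about 42% drop out of the base case. The article gives no 13- or 26-week rates. People who miss one form also tend to miss others, which moves the figure towards the 82% limit.
- **The populations overlap.** A reader might count the whole 18% as a mismatch with the clinical analysis. Most of it is common to both; only the extra exclusions in step 5 separate them.

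Two points stay open in the text. The Outcomes section lists GP record review as a source of resource use, so a missed resource-use form may not always exclude someone, although a missed utility form would. The article also does not say which data set feeds the acceptability curve.

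**Conclusion.** The point holds as one of analysis choice and labelling. The base-case CEA is a complete-case analysis under an intention-to-treat name, and the imputed analysis is placed second. At most about 290 of 354 participants could contribute, if the October 2021 loss of 18% applies to the final sample. About 232 to 276 would contribute if a further 5% to 20% of 52-week responders are incomplete, which is an assumption and not a figure from the documents.

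The case for change does not rest on proven bias. It rests on two things: the base case throws away interim costs and utilities that partial responders supplied, and it needs the more demanding of the two missing-data conditions. The planned imputed comparison makes this a change that should be made, not a flaw that invalidates the economic evaluation.

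**What to change.** In the Health economics section, before results are seen:

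- Make multiple imputation the base case for the ICER and the acceptability curve, with all randomised participants analysed as allocated. Impute separately by arm, with costs and utilities at each time point, baseline utility and the adjustment covariates in the model.
- Report the complete-case analysis as the sensitivity analysis, and call it complete-case, not intention to treat.

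Both analyses are already planned, so no new data are needed. The cost is slightly more programming to combine imputation with bootstrapping for the acceptability curve. The new base case relies on a missing-at-random assumption, which should be stated.
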